## Abstract

**Background:**

The economic and public health burden of fragility fractures of the hip in Germany is high. The likelihood of requiring long-term care and the risk of suffering from a secondary fracture increases substantially after sustaining an initial fracture. Neither appropriate confirmatory diagnostics of the suspected underlying osteoporosis nor therapy, which are well-recognised approaches to reduce the burden of fragility fractures, are routinely initiated in the German healthcare system. Therefore, the aim of the study FLS-CARE is to evaluate whether a coordinated care programme can close the prevention gap for patients suffering from a fragility hip fracture through the implementation of systematic diagnostics, a falls prevention programme and guideline-adherent interventions based on the Fracture Liaison Services model.

**Methods:**

The study is set up as a non-blinded, cluster-randomised, controlled trial with unequal cluster sizes. Allocation to intervention group (FLS-CARE) and control group (usual care) follows an allocation ratio of 1:1 using trauma centres as the unit of allocation. Sample size calculations resulted in a total of 1216 patients (608 patients per group distributed over 9 clusters) needed for the analysis. After informed consent, all participants are assessed directly at discharge, after 3 months, 12 months and 24 months. The primary outcome measure of the study is the secondary fracture rate 24 months after initial hip fracture. Secondary outcomes include differences in the number of falls, mortality, quality-adjusted life years, activities of daily living and mobility.

**Discussion:**

This study is the first to assess the effectiveness and cost-effectiveness/utility of FLS implementation in Germany. Findings of the process evaluation will also shed light on potential barriers to the implementation of FLS in the context of the German healthcare system. Challenges for the study include the successful integration of the outpatient sector as well as the future course of the coronavirus pandemic in 2020 and its influence on the intervention.

**Trial registration:**

German Clinical Trial Register (DRKS) 00022237, prospectively registered 2020-07-09

## Background

With increasing life expectancy in Germany, the number of people with age-associated progressive metabolic bone disease, so-called osteoporosis, rises steadily as well. Suffering from osteoporosis poses a tremendous risk for those affected to sustain bone fractures as a result of lowered bone density. According to the prevalence extrapolations of Hadji et al. (2013) [1], 6.3 million people in Germany suffer from osteoporosis and 885,000 new cases are expected to occur annually. Women aged 50 years or above are particularly prone to develop osteoporosis and, therefore, have a significantly higher lifetime risk of sustaining a major osteoporotic fracture (i.e. arm, hip and spine) compared with men [2].

In Germany, osteoporosis-related healthcare costs amounted to 4.5 billion Euros in 2009 [3]. Almost a decade later, osteoporosis-associated fractures were responsible for annual expenses of more than 11 billion Euros. Between 2017 and 2030, osteoporosis-induced healthcare costs are expected to increase further up to 14 billion Euros per year. Even though hip fractures represent a fifth of all fragility fractures, they make up half of the total fracture-related healthcare costs [2].

Fractures of the hip are considered to be the most studied osteoporosis-related bone fractures because of not only their high associated costs but also their great impact on patients’ survival rate and quality of life. For example, the likelihood of requiring long-term care is estimated to be four-fold after sustaining an osteoporosis-related hip fracture [4, 5]. Moreover, the overall risk of an individual suffering from any secondary fracture increases substantially after an initial injury [2].

The most likely cause of secondary fractures lies in underlying, untreated osteoporosis. Thus, to reduce the economic and public health burden of fragility fractures, appropriate diagnostic testing (e.g. bone mineral density) to confirm whether osteoporosis is the underlying root cause is essential in order to subsequently initiate adequate treatment to prevent future fragility fractures. The International Osteoporosis Foundation (IOF) [2], however, reported that neither appropriate diagnostics of the suspected underlying osteoporosis nor therapy such as measures of fall prevention and/or drug treatment are routinely initiated in German hospitals or, afterwards, in the ambulatory care sector. In fact, only 40% of all patients suffering from a fragility fracture in the high-risk group (women over 50 years) were found to receive appropriate diagnostics, leaving 60% of the patients unrecognised [6]. In addition, drug persistency of those women receiving treatment over a time frame of 2 years was found to be reduced to 40% or lower [7]. In 2018, only 20% of hip fracture patients (> 70 years, low-energy trauma) treated in German hospitals with certified orthogeriatric co-management (AltersTraumaZentrum DGU®) reported pre-fracture osteoporosis therapy; of these, 22% received specific medication [8].

International studies have shown that coordinated care models specifically designed for secondary fracture prevention, so-called Fracture Liaison Services (FLS), can lead to a substantial increase in appropriate assessment of the root cause and guideline-adherent therapy of fragility fractures, thus significantly reducing secondary fractures [9]. FLS have also been reported to be a cost-effective treatment option for hip fractures in Canada, Japan, the US and the UK. However, the FLS intervention varied substantially between countries [4].

## Objectives

FLS has not been implemented in German hospitals as a standard of care so far. However, because of the great burden of osteoporotic hip fractures combined with low preventive treatments, patients may benefit greatly from its implementation. Therefore, the overall objective of the study FLS-CARE is to test whether the coordinated care programme can close the care gap for patients suffering from a fragility hip fracture through implementation of systematic diagnostics and guideline-adherent interventions based on the FLS model.

The primary hypothesis (H_1_) is that, under the given circumstances of the German healthcare system, the implementation of FLS-CARE leads to a significant reduction in secondary fracture rates after initial hip fracture within a time frame of 2 years. Secondary hypotheses include that the implementation of FLS-CARE prevents falls (H_2_), lowers mortality (H_3_), increases quality of life (H_4_), patient satisfaction (H_5_) and therapy adherence (H_6_) and is a cost-effective intervention (H_7_).

## Methods

### Trial design

The study is set up as a non-blinded, cluster-randomised, controlled trial with unequal cluster sizes. Allocation to intervention group (FLS-CARE) and control group (usual care) follows an allocation ratio of 1:1 using hospitals (trauma centres) as the unit of allocation. In total, 18 study sites (9 hospitals per group) across Bavaria participated in the study. The cluster-randomised study design was chosen to avoid contamination bias by clinical staff and other patients within one centre.

For the purpose of this study, only trauma centres located in one federal state of Germany (Bavaria) are included.

### Study population and eligibility criteria

Out of 49 potentially suitable hospitals in Bavaria, 18 centres were recruited for the study through a letter of invitation. Hospitals were excluded from participation if a recent change in management occurred that could influence implementation of the study, if they failed to provide a letter of intent or refused to participate in the study (see Fig. 1).

**Fig. 1 Fig1:**
[figure not shown]
Flowchart of the FLS-CARE study. N_C_ refers to the overall number of trauma centres; n_P_ refers to the number of patients

The eligibility criteria for patients to participate in the study are as follows:

#### Inclusion criteria for patients

Insured by one of six participating sickness funds of the statutory health insurance (SHI), which are estimated to cover approximately 90% of the publicly insured Bavarian population (AOK Bayern, BARMER, DAK-Gesundheit, IKK Classic, BKK Mobil-Oil and Techniker Krankenkasse)Hip fracture near the joint (trochanteric fracture (AO type 31 A1–A3) or femoral neck fracture in the context of low-energy trauma (AO type 31 B1–B3, not C1–C3))Age ≥ 50 years for women and ≥ 60 years for menWritten informed consent

#### Exclusion criteria for patients

Any cancer diagnosisDialysis patientsPre-existing immobilityCurrently receiving specific osteoporosis therapyHigh-energy trauma

#### Identification of eligible patients

Depending on the study arm, either FLS-CARE or study nurses identify potential patients using pre-agreed protocols through the hospital information system (HIS). If the screening of eligible patients is successful, the nurse informs the attending physician who is responsible for obtaining informed consent. After receiving details of study participation, every patient has at least 24 h for consideration. Once enrolled in the study, the participant can withdraw within 2 weeks through their sickness funds without giving reasons and thereafter through a declaration of will [10]. Clear guidelines on the withdrawal process are provided for all participants at the time of enrolment.

### Intervention

The new form of healthcare delivery (FLS-CARE) is compared with usual care to assess both effectiveness and cost-effectiveness/utility of the intervention.

#### Intervention group

The FLS-CARE study intends to reduce the frequency of secondary fractures by targeting underlying osteoporosis as the root cause. The study programme includes a guideline-based care concept (FLS) in a network of multiple professionals (physicians, nurses and physiotherapists) from the inpatient and outpatient sectors. Specially trained FLS-CARE nurses play a central role in FLS-CARE as liaison partners for the sectors. They are responsible for guidance between hospital and ambulatory care and health literacy of the patients. They monitor patients’ adherence and ensure the conduct of intervention measures. The FLS-CARE nurses at the study centres, the participating GPs and medical specialists are educated on the principles of FLS and parameter collection for the study.

The FLS model for the patients of the FLS-CARE (intervention) group comprises four main modules:
*Diagnostics*: All patients receive an evidence-based diagnostic assessment based on the DVO guidelines [11] and the best practice framework of the IOF [12] during their hospital stay.*Education*: The FLS-CARE nurses highlight the importance of, for example, fall prevention and other physiotherapeutic exercises and motivate patients to follow up their goals for therapy to prevent secondary fractures and to enhance health literacy and behaviour. After discharge, the FLS-CARE nurses make domiciliary visits to assess and educate patients on individual fall risks. They also highlight the nearest support groups for patients suffering from osteoporosis as additional resources.*Therapy*: All patients receive medical and physical therapy as indicated, again in accordance with DVO and IOF guidelines. Treatment plans and adherence are regularly monitored by the FLS-CARE nurses.*Coordination*: The FLS-CARE nurses help to coordinate physical therapy sessions and follow-up appointments (3, 12 and 24 months post fracture) in the outpatient sector at certified GPs and/or medical specialists to ensure the continuity of specific care. In regular telephone calls, FLS-CARE nurses try to improve long-term adherence to therapy.

#### Control group

Participants in the control group will receive treatment as usual with follow-up appointments at identical intervals to the FLS-CARE group. Trained study nurses are responsible for contacting the patients and collecting study parameters from the control group to avoid potential biases.

All trauma centres treating the control group are prohibited from implementing any form of FLS during the study period to avoid potential bias. However, they are not forbidden to practise modules of FLS if they have already been implemented as a standard of care.

### Outcomes

The primary outcome measure of the study is the secondary fracture rate 24 months after initial hip fracture to see whether FLS-CARE serves as an effective tool for secondary prevention under the circumstances of the German healthcare system.

In addition, secondary outcomes, process indicators, health economic parameters and risk factors are collected and evaluated (see Table 1). Secondary outcomes include the absolute and relative number of falls after discharge, the mortality of patients (time to event), changes from baseline in quality-adjusted life years (QALY), activities of daily living (Barthel Index) and mobility (Parker Mobility Score). QALYs are calculated using the standardised EQ-5D-5L questionnaire from the EuroQol Group [13]. Satisfaction with the treatment of the fragility fracture is assessed from all participants after discharge and 24 months after initial fracture using a translated form of the standardised Short Assessment of Patient Satisfaction (SAPS) [14].

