### Data collection

All participants are interviewed at five points in time (see Table 1 and Fig. 1): directly after informed consent (t_0_), at discharge (t_1_), after 3 months (t_2_), 12 months (t_3_) and 24 months (t_4_) post fracture. For the FLS-CARE group, outcomes are collected by either outpatient physician or FLS-CARE nurses at the follow-up appointments (t_1–4_). Both outpatient physician and FLS-CARE nurse receive prior training in data collection from the FLS-CARE study group. For the control group, study nurses are responsible for data collection.

All follow-up appointments and outcomes are recorded in the specifically developed and highly standardised FLS-CARE tailored IT-based documentation, so-called FLS-CARE documentation modules, to promote data quality.

The FLS-CARE/study nurses also have access to diagnostic, therapy and process data through the aforementioned FLS-CARE documentation modules. They can monitor whether participants comply with follow-up schedules. If a patient does not appear at an appointment, the FLS-CARE/study nurse receives notification and can contact him or her by telephone. If he or she cannot or does not want to attend the follow-up appointment due, the FLS-CARE/study nurse tries to collect the study parameters by telephone.

Participation is not specifically promoted in the intervention group, other than mentioned above, in order to create results that are directly transferable to clinical routine. Missing data and related information are recorded as such in the FLS-CARE documentation modules.

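### Satisfaction (SAPS, H5) is at risk of bias towards FLS-CARE, because outcomes there are collected by staff who deliver the care and in the control arm by study nurses

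*Protocol article*

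**What the plan says.** The Objectives section lists better quality of life (H4) and patient satisfaction (H5) among the secondary hypotheses. Under Outcomes, SAPS is the satisfaction measure: "Satisfaction with the treatment of the fragility fracture is assessed from all participants after discharge and 24 months after initial fracture". The same section derives QALYs from EQ-5D-5L, and the Economic evaluation section uses utility values for the cost-utility ratio.

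The Data collection section gives the mode and the collectors. On mode: "All participants are interviewed at five points in time", namely after consent, at discharge, and at 3, 12 and 24 months. On collectors from discharge onwards: "For the FLS-CARE group, outcomes are collected by either outpatient physician or FLS-CARE nurses at the follow-up appointments", whereas "For the control group, study nurses are responsible for data collection". If a visit is missed, the FLS-CARE or study nurse tries to obtain the data by telephone.

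The Intervention group section shows that the FLS-CARE collectors also deliver the programme: "Specially trained FLS-CARE nurses play a central role in FLS-CARE as liaison partners for the sectors". These nurses educate patients, visit them at home, monitor adherence and coordinate follow-up, and "In regular telephone calls, FLS-CARE nurses try to improve long-term adherence to therapy". The participating GPs and specialists belong to the same care network. For the other arm, the Control group section says: "Trained study nurses are responsible for contacting the patients and collecting study parameters from the control group to avoid potential biases". The Allocation section states that neither participants nor nurses can be blinded.

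**The concern.** SAPS is a subjective rating of treatment, and the article names no external record against which it could be checked. Process indicators, by contrast, also draw on claims data. In the FLS-CARE arm the rating goes to a person who provided part of what is rated and who stays in contact with the patient. In the control arm it goes to a study nurse, for whom the article describes screening, contact and data collection but no treatment. People tend to be more generous when the listener has a stake in the answer, so the plausible direction for H5 favours FLS-CARE.

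The collector differs systematically by arm, so the H5 contrast mixes the effect of the programme with the effect of who asks. Covariate adjustment, mixed models and multiple imputation cannot separate the two, because no patient in either arm is assessed by the other arm's type of collector. It has to be solved when the data are collected.

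**Working it through.** **Step 1: set the sections side by side.**

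| Feature | FLS-CARE arm | Control arm |
|---|---|---|
| Collector from discharge to 24 months | Outpatient physician or FLS-CARE nurse | Study nurse |
| Collector delivers the programme under test | Yes | No such role described |
| Fallback after a missed visit | Telephone, FLS-CARE nurse | Telephone, study nurse |
| Collector blinded | No | No |
| Separation of collection from care given as a safeguard | None described | Study nurses, to avoid bias |

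The two SAPS assessments fall after discharge and at 24 months, so both lie in the period when the collectors differ. The article does not say whether SAPS and EQ-5D-5L are read out or filled in by the patient, and Table 1 is not shown.

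**Step 2: reproduce the protocol's own figure.** The Sample size section gives 507 per group for the primary outcome, from 3% versus 10%, 80% power, 5% significance, k = 9, ICC 0.01 and cv 1.37. A two-sided pooled comparison without continuity correction needs n_i = 194. The section's formula then gives

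n_C = 194 × 9 × 0.99 / [9 − 194 × (1.37² + 1) × 0.01] = 1728.54 / (9 − 5.581) = 505.6,

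which agrees with 507 within rounding. The design inputs are thus understood as the protocol uses them.

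**Step 3: illustrate what a collector effect could do to H5.** From the protocol: 608 per group, 20% drop-out, 9 clusters per group, ICC 0.01 and cv 1.37. Assumed here: a standardised continuous SAPS score, no true effect, a shift of 0.1 or 0.2 SD in one arm, a two-sided 5% test, and the primary outcome's ICC carried over to SAPS.

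- Evaluable per arm: 608 × 0.80 = 486. Mean cluster size: 486 / 9 = 54.
- Design effect: 1 + [(1.37² + 1) × 54 − 1] × 0.01 = 1 + (155.35 − 1) × 0.01 = 2.54.
- Effective size: 486 / 2.54 = 191 per arm.
- Standard error of the standardised difference: √(2 / 191) = 0.102.
- Shift 0.1 SD: 0.1 / 0.1023 = 0.98; P(|Z| > 1.96) is about 16%.
- Shift 0.2 SD: 0.2 / 0.1023 = 1.95; P(|Z| > 1.96) is about 50%.

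The nominal rate is 5%.

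**Step 4: vary the inputs that are least certain.**

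| n per arm | cv | ICC | Shift 0.1 SD | Shift 0.2 SD |
|---|---|---|---|---|
| 486 | 1.37 | 0.01 | 16% | 50% |
| 486 | 1.37 | 0.05 | 8% | 18% |
| 486 | 1.37 | 0.10 | 7% | 12% |
| 507 | 1.37 | 0.01 | 17% | 50% |
| 486 | 0.71 | 0.01 | 21% | 64% |

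The last row uses about the largest cv that the Recruitment section's cap of 104 per cluster permits when 608 patients are spread over 9 hospitals (five at 104, one at 88, three at zero). It is not a protocol assumption and is shown only as a sensitivity. The table shows how sensitive the H5 test is to a bias of assumed size. It is not evidence that such a bias exists.

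**The case against.** The strongest reply has five parts.

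- **Mode.** SAPS and EQ-5D-5L are described as standardised instruments, and the article does not say that they are read out. Interviewing and collecting are general terms that could cover handing over a form, and a condensed article may leave the mode to the full protocol. This stands as far as it goes: missing detail on mode is not the finding. The finding rests on what is stated, which is interview as the only described mode and a different type of collector in each arm. Even a self-completed form is exposed if it is handed back to the carer.
- **What SAPS rates.** It covers treatment of the fracture as a whole, including surgery and the hospital stay, and at the first assessment much of the outpatient support is still to come. This stands. The collector's own work is only part of what is rated, so the risk is probably larger at 24 months.
- **Quality of life.** A reader might infer that courtesy answers inflate both satisfaction and quality of life, in the FLS-CARE arm alone, and that this carries into the cost-utility ratio. The documents do not support that. EQ-5D-5L describes the patient's health and not the carer, and familiarity with a nurse could equally bring fuller reporting of problems. Unblinded study nurses who contact patients repeatedly may also receive some courtesy answers.
- **Importance.** Secondary outcomes are to be summarised descriptively and modelled only if appropriate. That limits the weight of the point but does not remove it, because H5 is stated as a hypothesis and a descriptive contrast carries the same bias.
- **Remedy.** Returning forms by post or online in a frail cohort, which the Sample size section likens to one with a mean age of 80, risks missing and proxy answers. Loss is already expected to be higher in the control group. This weighs against postal or online EQ-5D-5L, and much less against a sealed SAPS form.

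**Conclusion.** The concern holds in limited form. As written, the protocol has outcomes collected by care providers in one arm and by study nurses in the other. It gives bias avoidance as a reason for using study nurses in the control arm and describes no matching safeguard in the FLS-CARE arm. This puts H5 at risk of bias in favour of FLS-CARE that no analysis of these data can remove. For EQ-5D-5L, and so for H4 and the QALYs, the risk is lesser and indirect, and its size and direction are not shown.

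No magnitude can be taken from the documents. The figures of about 16% and 50% depend on assumed shifts of 0.1 and 0.2 SD, a continuous score, and the primary outcome's ICC of 0.01 applied to SAPS. They fall to 7% and 12% at ICC 0.10. The point concerns secondary outcomes and does not touch the fracture comparison. It should be corrected because the remedy is simple and must come before the data are collected.

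**What to change.** Amend the Outcomes and Data collection sections as follows.

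- **SAPS, both arms:** the patient completes the form, seals it, and it is returned directly to the evaluating institution. The FLS-CARE nurse, study nurse and outpatient physician do not see it.
- **EQ-5D-5L, both arms:** the patient completes it at the visit where able. Routine postal or online return is not asked for, because missing and proxy data could outweigh the gain.
- **Both forms:** record the mode of completion and any helper for each form, and run a sensitivity analysis by mode.

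If self-completion was always intended, stating it in these two sections, together with the return route for SAPS, would settle most of the point.

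The cost is printed forms and their return in both arms, with no extra staff. The downside is somewhat more missing or proxy-assisted SAPS forms among frail patients, possibly unequal between arms, so completeness and assistance should be reported by arm.
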